### Randomisation and blinding

Cluster-randomisation will be used with each childcare institution constituting a cluster, in order to avoid contamination within an institution between participating and non-participating workers. Participating childcare institutions will be randomised to either intervention or usual practice (i.e. wait-list control) arms of the trial. This randomisation will be conducted upon enrolment of each participating childcare institution into the study. The randomisation sequence has been developed using the statistical software R [27].

Because of the time needed for the childcare institutions to plan their participation in the trial, we need to inform them about their allocation to intervention or control group before the baseline data collection. Moreover, due to the nature of the trial, it will not be possible to blind neither the researchers nor the participating employees as regards whether a particular institution is subject to the intervention or not. However, allocation concealment will be maintained throughout the study, and all researchers conducting the randomisation, statistical analysis, and evaluation will be blinded.

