### Questionnaire

The questionnaires include a combination of items to assess the following descriptive factors of the study population, as well as potential confounders, and beneficial and adverse effects i) sociodemographic factors, i.e. age; sex; ethnicity; length of service; job title; and weekly working hours, ii) health and behaviours, i.e. musculoskeletal pain and pain-related work interference [28]; medicine use; smoking; general health [29, 30]; self-efficacy [31]; well-being [32]; and sleep behaviour [33], iii) self-rated physical capacity: cardiorespiratory fitness and muscle strength [34], iv) stress [35], and v) work environment factors, i.e. perceived physical exertion during work [36]; productivity [37]; psychosocial work environment [38]; single item work ability [39]; short-version perceived need for recovery [40]; and sickness absence and presenteeism [41, 42].

Need for recovery and productivity will act as secondary outcomes. Need for recovery will be determined using a short, three-item version: ‘At the end of my work day I am exhausted’; ‘I find it hard to show interest in other people, when I have just come home from work’; and ‘It takes me over an hour before I am fully recovered after a work day’. All items have five response categories: ‘Never’; ‘Rarely’; ‘Some of the Time’; ‘Most of the Time’; and ‘Always’ [40]. Productivity will be determined using one item: ‘On a scale from 0 to 10, where 0 is the worst job performance anyone could have at your job and 10 is the performance of a top worker, how would you rate your overall job performance on the days you worked during the past 4 weeks (28 days)?’ [47].

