### Statistical analysis

Evaluation of intervention effectiveness on the primary and secondary outcomes as well as the cost-effectiveness will be based on multilevel models, taking into account that the study design implies repeated measurements within each participant [57]. Conclusions about the effectiveness of the intervention with respect to the primary and secondary outcomes will be based on the group effect and its 95% confidence interval. The 95% confidence intervals for the incremental cost-effectiveness ratio will be estimated using bootstrapping (1000 bootstrap samples with replacement) [58]. All analyses will be performed according to the intention-to-treat principle [59]. Potential confounding factors (e.g. baseline differences between the intervention and control group in factors like age and BMI) will be adjusted for in the statistical analyses.

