The main limitation of the study is the lack of allocation concealment, which introduces the risk of selection bias. This is, however, inevitable since the study design requires the participating childcare institutions to make organisational changes that build on a participatory approach. Thus, the participating childcare institutions need to be informed of their allocation in advance, in order to facilitate their introduction of organisational changes as well as allowing them adequate time for preparing and initiating any required logistics, e.g. staffing issues or equipment. Also, blinding the participants is, for natural reasons, not possible. This is a common issue in participatory interventions, and it may introduce a risk of unintended effects, e.g. a possible placebo change in the selected outcome(s), or a Hawthorne effect [62]. However, we will try to minimise both of these limitations. All participants will, eventually, receive the intervention, participants are only informed about when the intervention will be implemented at their institution, and not whether they are allocated to an intervention or a control group in the actual intervention project. Thus, the lack of blinding is expected to have no or minimal influence on the results of the study.

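### Covariate adjustment is tied to baseline differences seen between the arms and the list is left open; it should be a short list fixed in advance

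*Protocol article*

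**What the plan says.** The covariate rule is one sentence in the Statistical analysis section: "Potential confounding factors (e.g. baseline differences between the intervention and control group in factors like age and BMI) will be adjusted for". It applies to the analyses in general, and the same section opens with "Evaluation of intervention effectiveness on the primary and secondary outcomes as well as the cost-effectiveness will be based on multilevel models", so the rule reaches the primary model. The trial's conclusions "will be based on the group effect and its 95% confidence interval", that is, on the output of the model that the rule shapes.

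The Questionnaire section describes its items collectively as covering "descriptive factors of the study population, as well as potential confounders, and beneficial and adverse effects". It does not say which of them would enter a model. No section names a final covariate set or says how large a difference must be to count.

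Two other statements bear on the point. Under Randomisation and blinding, institutions learn their arm early: "we need to inform them about their allocation to intervention or control group before the baseline data collection". The limitations section concedes the consequence: "The main limitation of the study is the lack of allocation concealment, which introduces the risk of selection bias".

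**The concern.** In a randomised comparison, a covariate earns its place by predicting the outcome. A difference between arms at baseline is a different criterion. It is partly chance, and here it may partly reflect who agreed to take part after the allocation was known. Using it to build the model has three consequences.

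- The model is not known until the baseline data have been examined, so the primary estimate can shift with judgements made at that stage.
- A strong predictor that happens to balance can be left out, while a variable unrelated to outcome can be put in because it happened to differ.
- The 95% confidence interval is computed as if the chosen model had been fixed all along.

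With about 14 clusters, visible imbalance in some variables would be unsurprising, so the rule is likely to come into use.

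An analysis plan that is not shown could properly supply a covariate list on which an article is silent. This article is not silent: it states a criterion, and an analysis plan would have to replace that criterion, not merely complete it.

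**Working it through.** **1. What can be computed.** The article's only computed design figure is the total of 132 participants. The point does not depend on it, and the fix leaves it unchanged. The article gives no threshold for a difference and no closed list of candidates. The expected number of chance imbalances therefore cannot be calculated without inventing both, and none is given here.

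**2. Does selecting on imbalance distort the error rate?** An illustrative simulation with no true intervention effect was run.

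Inputs from the Power calculation section:
- 14 clusters and ICC 0.05;
- cluster size 10 with 30% drop-out, giving 10 × (1 − 0.30) = 7 completers per cluster.

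Assumed inputs:
- 2 or 5 covariates, each with coefficient 0.3;
- a t-test on cluster means of covariate-adjusted residuals;
- selection of a covariate when its between-arm difference has p < 0.10;
- 6,000 runs.

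The Monte Carlo standard error near 0.05 is √(0.05 × 0.95 / 6000) = 0.0028.

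| Rule | 2 covariates | 5 covariates |
|---|---|---|
| List fixed in advance | 0.052 | 0.050 |
| Selected on imbalance, p < 0.10 | 0.041 | 0.035 |
| Most favourable model from the open list | 0.087 | 0.132 |

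A fixed list holds the nominal level. The mechanical imbalance rule falls below it by 0.009 and 0.015, about 3 and 5 Monte Carlo standard errors. Inflation appears only when the model is chosen by its result.

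**3. What is baseline adjustment worth?** The comparator matters, because the Primary and secondary outcomes section already evaluates change from baseline. Take equal variances (set to 1) at both times and correlation ρ between them, ignoring clustering:

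- variance of a change score: 2(1 − ρ);
- variance after adjusting for the baseline value: 1 − ρ²;
- proportional reduction: 1 − (1 − ρ²)/[2(1 − ρ)] = 1 − (1 + ρ)/2 = (1 − ρ)/2.

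The document does not give ρ. At an assumed ρ = 0.5 the variances are 1.00 and 0.75, a reduction of 25%. At ρ = 0.7 they are 0.60 and 0.51, a reduction of 15%. If the multilevel model already constrains the arms to a common baseline mean, the further gain is about nil.

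**The case against.** The strongest reply is that the baseline differences are offered as an example. The sentence sets out no significance test, no cut-off and no instruction to drop balanced variables, and it can be read as saying that age and BMI will simply be included. That milder reading is available. A reader might infer that the protocol prescribes baseline significance testing; the text does not support that. But on the milder reading the set is still open, and the only reason offered for adjusting is still a difference between arms.

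A reader might also infer that the rule inflates false positives. The simulation does not support this for a mechanical rule, which was conservative. The inflated figures need result-driven choice, which the article nowhere proposes.

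A third inference is that baseline outcome data are being ignored, at a large cost in precision. That fails too, since change from baseline and repeated-measures models are already planned.

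It can be said that blinding protects against choice, since "all researchers conducting the randomisation, statistical analysis, and evaluation will be blinded". This would limit choice by result if it holds, although the same section says that researchers cannot be blinded to an institution's status. Even with coded arms, imbalance between the two groups is visible, so blinding does not prevent selection on it.

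Finally, adjustment has a real rationale here. Allocation is disclosed before baseline, so differences may reflect differential participation and not chance alone. That stands as a reason to adjust. It supports a list chosen for prognostic value beforehand, not one assembled from the differences that appear.

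**Conclusion.** The concern holds as a fault in the stated criterion: adjustment is linked to observed baseline differences, the list is open, and the rule governs the primary and secondary models. The consequences are a data-dependent model, possible omission of prognostic covariates that happen to balance, and intervals that take no account of the selection.

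The size is moderate and rests on assumptions. The error rates come from an illustrative simulation whose covariate effects and selection threshold are not in the article. They show a departure from nominal in the conservative direction under a fixed rule, and room for inflation only under choice by result. The precision gain from baseline adjustment depends on an unstated correlation and on how the multilevel model treats the baseline. The point calls for a correction to the plan and does not show that the trial's result would be wrong.

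**What to change.** Replace the sentence with a short covariate list, fixed before any outcome analysis and applied whatever the observed balance, with no selection by comparing the arms at baseline. A reasonable list is the baseline value of the outcome analysed, age, sex and BMI. The baseline outcome can enter as a covariate or through a repeated-measures model with a common baseline mean. The choice should be stated, because the common-mean version assumes that the arms are alike at baseline, and recruitment after disclosure could strain that assumption. Any further adjustment prompted by an observed imbalance should be reported as a labelled sensitivity analysis.

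The cost is one sentence. All four variables are already collected (questionnaire, anthropometry and baseline outcome measurements), the sample size is unaffected, and the Trial status section describes the study as ongoing. The downside is that a chance imbalance in an unlisted variable is handled only in the sensitivity analysis.

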## Discussion

This will be the first randomised controlled trial to evaluate the effectiveness of the Goldilocks work principle in terms of increased work time in MVPA and better cardiorespiratory fitness for workers. If successful, the study will demonstrate that the Goldilocks work principle has a potential to improve health and physical capacity among workers while performing productive work. A scaling of the Goldilocks work principle to other occupations and countries could have a large impact on general health and social justice of working populations [12].

### Strengths and limitations of the study

A methodological strength of the study is the use of a cluster randomised design, which minimises the risk of contamination within and between institutions in the intervention and control groups. Another methodological strength is the application of a systematic participatory approach involving the end users throughout the entire process. We will collect experiences and information during the process of developing and tailoring the intervention, and this can likely benefit the present as well as future studies. Even the use of wearable accelerometers and heart rate monitors for measuring the primary outcomes is a strength. By using wearable sensors rather than self-reported methods to record the primary outcome, bias introduced by self-reports, e.g. due to lack of blinding of participants or inaccurate perception [60], is considered minimal.

In addition, utilizing CoDA is a strength of this study, since it allows the co-dependency between work time spent in different behaviour types (sedentary behaviour; light physical activity; MVPA) to be taken into account. Thus, the use of CoDA represents an approach that gives a better understanding of the potential effect of an intervention from a whole-workday perspective than if each behaviour is analysed as an independent factor [56, 61]. Furthermore, conducting a process evaluation is a strength of this study. The process evaluation provides an opportunity for thoroughly evaluating the implementation of the intervention and identify why the intervention may or may not be effective.

The main limitation of the study is the lack of allocation concealment, which introduces the risk of selection bias. This is, however, inevitable since the study design requires the participating childcare institutions to make organisational changes that build on a participatory approach. Thus, the participating childcare institutions need to be informed of their allocation in advance, in order to facilitate their introduction of organisational changes as well as allowing them adequate time for preparing and initiating any required logistics, e.g. staffing issues or equipment. Also, blinding the participants is, for natural reasons, not possible. This is a common issue in participatory interventions, and it may introduce a risk of unintended effects, e.g. a possible placebo change in the selected outcome(s), or a Hawthorne effect [62]. However, we will try to minimise both of these limitations. All participants will, eventually, receive the intervention, participants are only informed about when the intervention will be implemented at their institution, and not whether they are allocated to an intervention or a control group in the actual intervention project. Thus, the lack of blinding is expected to have no or minimal influence on the results of the study.

### Trial status

The study is ongoing. Recruitment of childcare institutions opened in March 2019 and will continue until all childcare institutions required for the trial are enrolled, planned to be September 2020. The intervention will start at the first enrolled childcare institutions in January 2020. For the last childcare institutions enrolled in the trial, the intervention is planned to start September 2020. We will finalize the intervention for the last group of childcare institutions in December 2020.

## Data Availability

Not applicable.

## Abbreviations

CoDA: Compositional data analysis
CONSORT: Consolidated standards of reporting trials
HR _sleep_: Sleeping heart rate
HR: Heart rate
HR_max_: Estimated maximal heart rate
HRR: Heart rate reserve
ilr: Isometric log-ratio
ISRCTN: International Standard Registered Clinical/soCial sTudy Number
MVPA: Moderate to vigorous physical activity
SD: Standard deviation
SPIRIT: Standard protocol items: recommendations for interventional trials
TIDieR: Template for intervention description and replication
Trio: Collective term for group consisting of a manager, a union representative, and an occupational health and safety representative
VO_2max_: Maximal oxygen consumption
WECoCM: The Work Environment Consultancy of Copenhagen Municipality
